### Study site: clusters and characteristics of the clusters

The study will be conducted in Muang district, Chiang Rai, the northernmost province of Thailand. Every health center within the study site district, which has a hypertension and diabetes clinic, will be screened for eligibility criteria. In order to prevent an empty cluster, any health center with a total of fewer than 200 patients attending the hypertension and diabetes clinic will not be included. In this study, one health center will form one cluster. Each cluster will have 100 participants, and there will be four clusters in each study arm. The locations of randomly allocated clusters are as shown in Figure
1. The study has been carefully designed to minimize the coefficient of variation among the clusters.

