### Sample size

For a conventional randomized control trial, a total of 240 participants, randomizing 120 into each arm, will have enough power (90%) to detect the minimal difference of systolic blood pressure 130 (±20) and 120 (±20) mmHg, diastolic pressure 90 (±20) and 80 (±20) mmHg, difference in 24-hour estimated salt intake 10 (±5) and 8 (±4) g/day and CVD event rate of 0.15% and 0.08% between the control and intervention group with a 95% confidence interval
[6,31]. The cluster randomized trial design used in RESIP-CVD might result in loss of power and reduced efficiency. In this cluster randomized trial, the number of participants in each cluster will be the same, and other variable factors such as geography, food tradition, race and dietary habits are assumed not to be different for delineating the intracluster coefficient. To compensate the design effect, the inflation factor has been calculated by the formula (*Deff* = 1 + (*m–1*)*ρ*) where *Deff* is inflation factor for design effect, *m* is the size of each cluster, which is 30 and *ρ* is the intracluster coefficient which is assumed to be 0.07. The sample required for a cluster randomized trial was inflated to 720. With a loss to follow-up of approximately 10%, we expect that the sample size of 800 patients will yield sufficient power to detect the desired minimal difference in primary and secondary outcomes between the intervention and control group. All eight clusters of the RESIP-CVD study will enroll 100 eligible participants.

We identified the confounders and planned to collect the information for multivariate analysis adjustment. (Table
4)

**Table 4 T4:** Confounder measurements

**Confounder**	**Variables**	**How to measure**
Demographic characteristics	Age, sex, social status, family size, educational attainment, occupational history, income	Questionnaire
Lifestyle	Smoking, alcohol	Questionnaire
Genetic factor	Family history of diabetes/hypertension	Questionnaire
Drugs	Different medications for diabetes and hypertension	Clinical record

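### The design effect is computed for clusters of 30, but the trial enrols 100 in each of 8 clusters; on its own inputs, power for the 10 mmHg systolic difference is about 55%, not 90%

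*Protocol article*

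**What the plan says.** The Sample size section of the protocol article starts from an individually randomised trial of 240 patients, 120 per arm, which "will have enough power (90%) to detect the minimal difference of systolic blood pressure 130 (±20) and 120 (±20) mmHg". The same 240 is said to cover "diastolic pressure 90 (±20) and 80 (±20) mmHg" and a "difference in 24-hour estimated salt intake 10 (±5) and 8 (±4) g/day", among other targets.

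The section then allows for clustering with Deff = 1 + (m − 1)ρ. It states that m "is the size of each cluster, which is 30 and" sets ρ, the intracluster coefficient, at 0.07. The result is given as 720, raised to 800 for about 10% loss to follow-up. On that basis, "we expect that the sample size of 800 patients will yield sufficient power to detect the desired minimal difference" in the primary and secondary outcomes.

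The section ends by stating: "All eight clusters of the RESIP-CVD study will enroll 100 eligible participants". The study-site section agrees: "Each cluster will have 100 participants, and there will be four clusters in each study arm".

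**The concern.** In the design-effect formula, m is the number of patients per randomised cluster. The section defines it that way, gives it the value 30, and closes by fixing the cluster size at 100. The 30 matters because the stated total of 720, and so 800, comes directly from it. At m = 30, 720 patients would be 720/30 = 24 clusters; this trial has eight.

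At fixed ρ, 24 clusters of 30 carry far more information than eight clusters of 90 or 100, because between-center variation is averaged over three times as many centers. Four clusters per arm also leave only 8 − 2 = 6 degrees of freedom for a cluster-level comparison, which a design effect alone does not account for.

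The risk is in how the result is read. If the trial is believed to have 90% power, a null result will be taken as evidence that the education program does not lower blood pressure. With roughly even odds of detecting the target difference, a null result would not support that reading.

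**Working it through.** **Inputs, all from the Sample size and study-site sections.** Systolic difference δ = 130 − 120 = 10 mmHg, SD 20. Salt 10 (SD 5) versus 8 (SD 4) g/day, so δ = 2. Two-sided α = 0.05, read from the 95% confidence interval. ρ = 0.07. Eight clusters, four per arm, 100 enrolled each; 10% loss leaves 90 per cluster, or 360 per arm.

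**1. Reproducing the plan's total.**
- Deff = 1 + 29 × 0.07 = 3.03
- 240 × 3.03 = 727, close to the stated 720 (240 × 3)
- 720 / 0.9 = 800

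The plan's figures therefore come from m = 30.

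**2. The same chain with the actual cluster size.**
- m = 100: Deff = 1 + 99 × 0.07 = 7.93; 240 × 7.93 = 1,903
- m = 90: Deff = 1 + 89 × 0.07 = 7.23; 240 × 7.23 = 1,735 completers, or 1,735.2 / 0.9 = 1,928 enrolled

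**3. Effective sample size, 90 retained per cluster.** 360 / 7.23 = 49.8 per arm, against the 120 the plan carries forward. For 90% power on systolic pressure alone, about 85 per arm would do (normal approximation).

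**4. Systolic power.**
- SE = √(2 × 20² × 7.23 / 360) = 4.01 mmHg
- Noncentrality = 10 / 4.01 = 2.49
- Noncentral t on 6 df: 55.2%
- Normal reference: 70.4%
- Simulated t tests on cluster means (200,000 trials): 55.5%

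Taking all 100 per cluster as retained changes little: 55.7% (t) and 70.9% (normal). Diastolic pressure has the same δ and SD, so the same figures apply.

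**5. Salt intake power.**
- SE = √((5² + 4²) × 7.23 / 360) = 0.907 g/day
- Noncentrality = 2 / 0.907 = 2.20
- Power: 45.7% (t, 6 df) or 59.6% (normal)

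**6. What the plan's arithmetic describes.** For 24 clusters of 30 at ρ = 0.07, systolic power is 95.7% (t, 22 df) or 97.1% (normal). The calculation works for that design, which is not this trial.

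**7. What eight clusters can deliver.** At ρ = 0.07 and 90 per cluster, the systolic difference detectable with 90% power is 15.7 mmHg (t) or 13.0 mmHg (normal). For 90% power at 10 mmHg, ρ must be at most about 0.022 (t) or 0.037 (normal). Larger clusters do not help: the effective total cannot exceed 8 / 0.07 = 114.

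**8. Sensitivity to the ICC** (systolic pressure, 10 mmHg, four clusters of 90 per arm):

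| ρ | Deff | Power, t on 6 df | Power, normal |
|---|---|---|---|
| 0.01 | 1.89 | 98% | 99.8% |
| 0.03 | 3.67 | 83% | 94% |
| 0.05 | 5.45 | 67% | 82% |
| 0.07 | 7.23 | 55% | 70% |
| 0.10 | 9.90 | 43% | 57% |

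**The case against.** Nobody can defend m = 30 against 100 per cluster; the case on the other side is about size.

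- **Reference distribution.** The plan uses only a design effect on a conventional sample size. Correcting m within that method gives 70% for systolic pressure and 60% for salt; the 6-df reference is an addition. The Analysis plan also names individual-level comparisons, and the abstract mentions multilevel regression. This stands to the extent that both figures should be reported. However, the Analysis plan includes a cluster-level analysis, and with four clusters per arm the t reference is the valid one. A normal reference overstates power here, and 70% is still well short of 90%.
- **Where the 90% sits.** It is attached to the 240-patient trial; the 800 are only called sufficient. Literally true. But the inflation is made to compensate for clustering, so its purpose is to preserve that power.
- **The comparator of 120.** For systolic pressure alone about 85 per arm give 90%, and 120 give about 97%. So 1,903 is the plan's own chain, not the systolic minimum, which would be 170 × 7.93 = about 1,350. This stands as a clarification. The power figures do not use the 240.
- **Baseline information.** The outcome is described as blood pressure change, and adjustment could raise power. The protocol article gives no correlation. As an assumption only, if adjustment cut the variance by 1 − r² at the same ICC, r = 0.5 gives about 67% (t) or 82% (normal), and r = 0.7 about 83% (t). This is a real mitigation, but the Analysis plan names a Student's t or non-parametric test on 1-year means, and baseline pressure is not in the confounder table.
- **Feasibility.** Only eight centers met the criterion and recruitment has begun. That limits the remedy; it does not make the stated power right.

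**Conclusion.** The concern holds. The cluster size in the design effect contradicts the design stated in the same section, and the claim that 800 patients are sufficient fails on the plan's own inputs. Power is about 55% for a 10 mmHg systolic (or diastolic) difference and about 46% for 2 g/day of salt, or 70% and 60% by the more lenient normal approximation.

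These figures assume ρ = 0.07, the stated SDs, 90 of 100 patients retained per center, equal clusters and an unadjusted comparison of 1-year means. They depend strongly on ρ: the plan would be adequate for systolic pressure if the true ICC were about 0.02 or less, but the plan itself chose 0.07. The correction must be made before the stated power is used to interpret a result.

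**What to change.** In the Sample size section:

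1. Replace m = 30 by m = 100 (90 after 10% loss) and state Deff = 7.93 (7.23).
2. Restate power for eight clusters on 6 df at ICC 0.07: about 55% for 10 mmHg systolic and about 46% for 2 g/day of salt, with the normal-approximation values of 70% and 60% alongside. Give the systolic difference detectable at 90% power as about 15.7 mmHg (13.0 normal).
3. Add a short ICC sensitivity table such as the one above.
4. Delete the claim of sufficient power for the primary and secondary outcomes.

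To recover part of the loss, a baseline-adjusted comparison that respects clustering could be specified. It would be a new element of the Analysis plan, and its gain should be quoted only with a stated assumption for the baseline correlation.

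The cost is a rewording and a less favourable stated power. No extra patients or centers are requested, and the intervention and visits are unaffected.

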### Data collection and follow-up

Before starting data collection, we completed feasibility surveys at the study site clusters. A pilot intervention was tested at a non-eligible health center. The timeline of the data collection and assessment will be formatted as seen in Table
1.

### Baseline survey

In this CRT, we wanted to test the health intervention in high-CVD-risk patients. A low incidence of CVD events in low-CVD-risk patients may warrant a larger sample size than that we calculated and a longer follow-up than we can perform. Therefore, we will recruit only the high-CVD-risk patients stratified by using the Framingham general CVD risk scoring system (10-year risk). Calculation of the Framingham score will require information such as age, sex, smoking status, systolic blood pressure, history of taking antihypertensive drugs, history of diabetes and body mass index (BMI).

After recruitment, the Framingham score of the eligible patients will be assessed in a baseline survey
[19,20]. The risk score calculator in formula excel spread sheet published by the Framingham Heart Study will be distributed to the study site HCs
[32]. HC staffs will be trained to apply it for the CVD risk stratification.

### Follow-up plan

The staffs of the health centers will be reinforced with additional staff from the research project. The research team will call patients who failed to visit the health center for the assessment. The research nurse in charge will visit the patient’s house and collect the urine sample if the participants are unable to come to the health center on the appointed date for assessment. The control arm participants will not have measurements as frequently as the intervention group participants. At the health center level, nurses are the main persons to follow up the patients and deliver the drugs. Patients are usually referred to the district hospital or regional hospital whenever there is poor control of their disease or they have problems such as a poor control of BP or blood glucose level or any symptoms suggestive of CVD. We will use this routine health system process to strengthen the follow-up.

### Analysis plan

The intention-to-treat analysis will be followed. The mean blood pressure and mean daily salt intake of both the intervention and control arms will be compared at the individual level at the 1-year follow-up using Student’s *t* test or the non-parametric test based on distribution. The analysis will be carried out at both the cluster and individual levels. The CVD incidence rate will be compared by time-to-event analysis. A structural equation modeling analysis will be used to determine the behavioral change predictors. Information such as the self-efficacy, stage of attitudinal change, decisional balance, family support, health center support, ready-made meals usage and cooking utensils will be collected by questionnaires and analyzed by the SEM (Figure
4).

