**Methods/Design:**

This is a cluster randomized trial. A total of 800 high-CVD-risk patients attending diabetes and hypertension clinics at health centers in Muang District, Chiang Rai province, Thailand, will be studied with informed consent. A health center recruiting 100 participants is a cluster, the unit of randomization. Eight clusters will be randomized into intervention and control arms and followed up for 1 year. Within the intervention clusters the following will be undertaken: (1) salt content in the daily diet will be measured and shown to study participants; (2) 24-hour salt intake will be estimated in overnight-collected urine and the results shown to the participants; (3) a dietician will assist small group health education classes in cooking meals with less salt. The primary outcome is blood pressure change at the 1-year follow-up. Secondary outcomes at the 1-year follow-up are estimated 24-hoursalt intake, incidence of CVD events and CVD death. The intention-to-treat analysis will be followed.

Blood pressure and estimated 24-hour salt intake will be compared between intervention and control groups at the cluster and individual level at the 1-year follow-up. Clinical CVD events and deaths will be analyzed by time-event analysis. Retinal blood vessel calibers of CVD-risk patients will be assessed cross-sectionally. Behavioral change to reduce salt intake and the influencing factors will be determined by structured equation model (SEM). Multilevel regression analyses will be applied. Finally, the cost effectiveness of the intervention will be analyzed.

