## Methods/Design

### Study objectives

The primary objective is to compare the effectiveness of health education via visualization of salt content in food, soup and urine, with routine health education by means of measuring blood pressure changes in high-CVD-risk patients at 1-year follow-up.

The secondary objectives are: to compare the effectiveness of specially designed health education with routine health education by means of monitoring estimated daily salt intake using urine sodium measurement, CVD incidence and retinal vessel caliber changes among diabetic and hypertension patients with high CVD risk. We will also compare the cost-effectiveness of health education via visualization of salt content in food, soup and urine with routine health education among diabetic and hypertensive patients with high CVD risk.

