### Study outcome and outcome measurements

#### Primary outcome

Blood pressure measurements will be used as the primary outcome of the study. Blood pressure will be measured serially at baseline and on the 3-, 6- and 12-month follow-up visits of the trial (Table
3). It will assess the impact of salt reduction on cardiovascular health. The HEM-907 IntelliSense professional digital blood pressure monitor (Omron Healthcare Inc., Lake Forest, IL, USA) will be used to measure blood pressure (Table
3).

**Table 3 T3:** Study outcome, outcome measurement and assessment methods

**Outcome**	**Assessment**	**Outcome measure**
Primary	Blood pressure	Omron HEM-907 IntelliSense professional digital blood pressure monitor
Secondary	Individual salt intake estimate/24-hour	Overnight urine collection and measurement of urine sodium using the KME-03 (average of 3 successive days’ measurements)
Clinical	CVD risk	General Framingham score 10-year risk
	CVD incidence	Diagnosis of each CVD event and CVD death
	Surrogate outcome	Retinal vessel caliber

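### The primary outcome is defined as blood pressure change, but the only test named for it compares 1-year means and makes no stated use of baseline

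*Protocol article*

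**What the plan says.** The Abstract (Methods/Design) states: "The primary outcome is blood pressure change at the 1-year follow-up". Study objectives likewise compares the arms "by means of measuring blood pressure changes in high-CVD-risk patients at 1-year follow-up". The Primary outcome section is looser: "Blood pressure measurements will be used as the primary outcome of the study". It names neither systolic nor diastolic pressure, and neither change nor level.

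The Analysis plan assigns the test: "The mean blood pressure and mean daily salt intake of both the intervention and control arms will be compared", and this is done "at the individual level at the 1-year follow-up using Student’s" t test or a non-parametric alternative. No change score or baseline term appears. It adds: "The analysis will be carried out at both the cluster and individual levels".

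Two other statements bear on adjustment. The Abstract says "Multilevel regression analyses will be applied", without naming an outcome or covariates. The Sample size section says "We identified the confounders and planned to collect the information for multivariate analysis adjustment" and points to Table 4, which lists demographics, smoking and alcohol, family history, and medications. Baseline blood pressure and baseline salt intake are not in it. Table 1, which covers both arms, schedules both at month 0.

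**The concern.** Change from baseline and 1-year level are different estimators. Their standard errors differ, and with only eight health centres they can give visibly different answers from the same data. As the sections stand, the primary result could be computed either way, and no section says which is the primary one.

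The choice matters more here than in an individually randomized trial. Four centres per arm are allocated by simple randomization, with no matching or stratification stated, so the arms can differ at baseline by an amount that is not small beside the target effect. A 1-year comparison that ignores baseline carries the persistent part of that difference into the estimate. The variable that could remove it is already collected, but no section commits to using it.

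**Working it through.** **Inputs.** From Sample size: systolic SD 20 mmHg, target difference 10 mmHg (130 against 120), intracluster coefficient (ICC) 0.07, loss about 10%. From Study site: 100 participants per cluster, 4 clusters per arm. Significance level 0.05, taken as two-sided. Not in the document: r, the correlation between baseline and 12-month cluster means.

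**The plan's own figure.** Deff = 1 + (30 − 1) × 0.07 = 3.03, and 240 × 3.03 = 727 against the stated 720 (1% apart). Then 720 / 0.90 = 800. The inputs are therefore read as the protocol meant them. The cluster size of 30 in that formula, against 100 enrolled, is a separate matter. The steps below use the actual size.

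**Chance baseline difference between arms.** With k clusters per arm of size m:

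SD of difference = √[2 × SD² × (ICC + (1 − ICC)/m) / k]

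= √[2 × 400 × (0.07 + 0.93/100) / 4] = √(14 + 1.86) = 3.98 mmHg.

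Under a normal approximation, the chance of an imbalance above 4 mmHg is 32%, and above 5 mmHg 21%. Had 800 people been individually randomized, the SD would be 20 × √(2/400) = 1.41 mmHg.

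Sensitivity (m = 100):

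| SD | ICC | SD of difference, mmHg |
|---|---|---|
| 20 | 0.02 | 2.4 |
| 20 | 0.05 | 3.4 |
| 20 | 0.07 | 4.0 |
| 20 | 0.10 | 4.7 |
| 15 | 0.07 | 3.0 |

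On average, a fraction r of a baseline imbalance persists at 12 months. With r = 0.6, a 4 mmHg imbalance carries 2.4 mmHg into the unadjusted comparison.

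**Power without baseline.** Cluster-level t test, 90 per cluster after loss: SE = √[200 × (0.07 + 0.93/90)] = 4.01 mmHg. With 6 degrees of freedom, power for 10 mmHg is 55%.

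**Power with baseline, cluster-level ANCOVA (5 degrees of freedom).** If the slope were known, SE would be 4.01 × √(1 − r²). The slope has to be estimated from eight means, which inflates the expected variance by 1 + 1/(2k − 4) = 1 + 1/4 = 1.25. The last column was obtained by simulating the eight cluster means.

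| r | SE, slope known | Power, slope known | SE × √1.25 | Power, slope estimated |
|---|---|---|---|---|
| 0.5 | 3.47 | 64% | 3.88 | 57% |
| 0.6 | 3.21 | 70% | 3.59 | 63% |
| 0.7 | 2.86 | 80% | 3.20 | about 73% |
| 0.8 | 2.40 | 91% | 2.69 | 85% |

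The variance breaks even with the unadjusted test when 1.25 × (1 − r²) = 1, that is r = 0.45. Simulated power is 53% at r = 0.4 and 50% at r = 0.3, both below 55%.

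**Plain change score.** SE = 4.01 × √[2(1 − r)]. This equals 4.01 at r = 0.5 and is larger below that, so moving from means to simple change gains nothing unless r exceeds 0.5.

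**The case against.** Several points on the other side are sound.

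- **A reader might infer that the trial plans only an unadjusted analysis.** The document does not support that. It promises multilevel regression, multivariate adjustment and a cluster-level analysis. What stands is narrower: the t test is the only method tied to blood pressure, and none of the others mentions baseline.
- **A reader might take Table 4 as proof that baseline is excluded from the models.** Table 4 lists confounders and how to measure them; it is not a model specification. A full covariate list may properly sit in an analysis plan that is not shown. The omission therefore supports the point but does not carry it. The mismatch between outcome and named test is in the text itself.
- **Change and 1-year level target the same between-arm effect under randomization.** This is true, so the sections do not conflict over what is being estimated. They leave open how it is estimated and with what precision.
- **Chance imbalance is not bias.** A valid cluster-level test already carries the 4 mmHg in its standard error. An individual-level t test does not, but that is a clustering defect distinct from this one.
- **A reader might expect adjustment to lift power to 64–80% or more for r between 0.5 and 0.7, at the price of one degree of freedom.** That holds only with a known slope. Estimating it from eight means gives 57–73%.
- **A reader might add a multiplicity charge, since systolic and diastolic pressure are both sized.** An error rate of 8–9% follows only if success on either counts and their correlation is 0.6–0.8. The document states neither, so this is a side issue.

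**Conclusion.** The point holds as an inconsistency with a cheap remedy. The Abstract and objectives define the outcome as change, while the only named test compares 1-year means with no stated role for baseline.

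The size is a chance baseline systolic difference with an SD of about 4.0 mmHg, 40% of the 10 mmHg target. This assumes that the protocol's SD of 20 and ICC of 0.07 apply at baseline; at an ICC of 0.02 it is 2.4 mmHg. The consequence is imprecision, and an estimate that can mislead given the imbalance actually observed. It does not make the trial's estimate systematically wrong.

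The power benefit is conditional. Relative to 55%, it is about 2 points at r = 0.5 and about 30 points at r = 0.8 for cluster-level ANCOVA, and negative at r of about 0.4 or less. No power was calculated for a mixed model with individual baselines.

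**What to change.** Make the Abstract, Study objectives, Primary outcome and Analysis plan name one primary estimate: the between-arm difference in 12-month systolic pressure, adjusted for baseline systolic pressure, in an analysis that respects clusters. Two forms would do: a mixed model with each participant's baseline systolic pressure and small-sample degrees of freedom, or ANCOVA on cluster means. Choose between them before outcome data are seen. Analyse diastolic pressure the same way as a secondary outcome, adjust salt intake for baseline salt intake, and list both baselines among the adjustment variables. Replacing means with a simple change score would align the wording, but improves precision only if r exceeds 0.5.

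No new data are needed; the change is to wording. The statistical cost of cluster-level ANCOVA is one degree of freedom plus the variance of a slope estimated from eight means, so the choice should rest on a stated, justified value of r.

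### As named, the 12-month t or rank test for blood pressure makes no use of the roughly 80 of 800 patients expected to lack that reading, although their earlier readings are scheduled; a mixed model would use them

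*Protocol article*

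**What the plan says.** - **Principle.** The Analysis plan opens with "The intention-to-treat analysis will be followed".
- **Named comparison.** The next sentence says that mean blood pressure and mean daily salt intake "will be compared at the individual level at the 1-year follow-up using" Student's t test or a non-parametric test, depending on the distribution.
- **Other analyses.** The Analysis plan adds "The analysis will be carried out at both the cluster and individual levels", and the Abstract (Methods/Design) adds "Multilevel regression analyses will be applied". Neither sentence gives time points or says whether readings before month 12 enter the model.
- **Endpoint.** The Abstract says "The primary outcome is blood pressure change at the 1-year follow-up".
- **Readings scheduled.** Under Primary outcome: "Blood pressure will be measured serially at baseline and on the 3-, 6- and 12-month follow-up visits of the trial". Table 1 marks blood pressure at every month from 0 to 12.
- **Expected loss.** Under Sample size: "With a loss to follow-up of approximately 10%, we expect that the sample size of 800 patients will yield sufficient power".
- **Follow-up.** The Follow-up plan provides for calls to absentees and for home visits, the latter described for urine collection only. It says "Patients are usually referred to the district hospital or regional hospital whenever there is poor control of their disease" and adds that this routine process will be used to strengthen follow-up. It also says that control participants are measured less often than intervention participants.

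**The concern.** A two-sample t or rank test at one time point cannot score a patient who has no value at that time. The same holds if the test is run on change from baseline, because change also needs the 12-month value. Means per health centre built from the same 12-month readings would inherit the gap.

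Patients who drop out after month 3 or month 6 leave blood pressures behind, and the named test sets these aside. If those who leave had higher or lower earlier pressures, in different proportions by arm, the arms compared at month 12 are no longer the arms that were enrolled. The article gives some reasons why loss might not be random. Poor blood pressure control leads to referral, contact is less frequent in the control arm, home visits are described for urine only, and patients who die have no 12-month value. None of these shows that biased loss will occur. They show only that it cannot be ruled out.

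At stake is a modest bias in the primary estimate, reported under an intention-to-treat label.

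**Working it through.** **1. The plan's own figures (Sample size).**
- Design effect: 1 + (30 − 1) × 0.07 = 3.03.
- 240 × 3.03 = 727, against a stated 720 (within 3%).
- Allowance for loss: 720 / (1 − 0.10) = 800, which matches exactly.
- Expected without a 12-month reading: 0.10 × 800 = 80.

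**2. Does leaving them out cost power?** Inputs from Sample size: systolic difference 10 mmHg, SD 20, intracluster coefficient 0.07, four centres per arm. Two-sided 5% is assumed. Effective n per arm = 4m / [1 + (m − 1) × 0.07].

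| Patients per centre | Design effect | Effective n per arm | Power, normal | Power, t on 6 df |
|---|---|---|---|---|
| 90 | 7.23 | 49.8 | 70.4% | 55.2% |
| 100 | 7.93 | 50.4 | 70.9% | 55.7% |

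The gain is about half a percentage point, so any case for change rests on bias. (The design effect here uses the enrolled centre size; that the plan's calculation uses 30 is a separate matter.) With 90 per centre the standard error of the difference is 20 × √(2 / 49.8) = 4.0 mmHg.

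**3. Possible bias.** The documents give no loss mechanism and no correlation between visits, so these are assumptions: 10% lost overall; loss depends only on month-6 systolic pressure; month-6 and month-12 values are bivariate normal with SD 20 and correlation ρ from 0.4 to 0.8; the month-12 means are 130 and 120; the month-6 difference is 5 or 10 mmHg.

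In each arm the mean at month 12 among those retained shifts by ρ × s, where s is the shift in the month-6 mean caused by the loss. So:

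difference among attenders = 10 + ρ × (s_control − s_intervention)

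| Assumed loss | Month-6 difference | s, control | s, intervention | Difference, ρ = 0.4 | Difference, ρ = 0.8 |
|---|---|---|---|---|---|
| Odds ratio 2 per 20 mmHg | 5 | −1.42 | −1.23 | 9.9 | 9.8 |
| Odds ratio 2 per 20 mmHg | 10 | −1.51 | −1.13 | 9.8 | 9.7 |
| Odds ratio 3 per 20 mmHg | 5 | −2.15 | −1.76 | 9.8 | 9.7 |
| Odds ratio 3 per 20 mmHg | 10 | −2.35 | −1.56 | 9.7 | 9.4 |
| Highest 10% all lost | 5 | −4.60 | −3.17 | 9.4 | 8.9 |
| Highest 10% all lost | 10 | −5.24 | −2.46 | 8.9 | 7.8 |

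For the last row at ρ = 0.8: 10 + 0.8 × (−5.24 + 2.46) = 7.8. The shift is at most about 0.6 mmHg under mild dependence and about 2.2 mmHg in the extreme case. Simulation under the same assumptions agrees, and regression on the month-6 value returns about 10.

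**4. The other direction.** If attenders show 10 mmHg and the lost tenth of each arm had a true effect of 5, 0 or −5 mmHg, the effect in all enrolled is 0.9 × 10 + 0.1 × 5 = 9.5, or 9.0, or 8.5 mmHg.

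**The case against.** **No completer set is stated.** A reader might infer that the article restricts the primary analysis to patients with a 12-month reading, and so contradicts its own intention-to-treat statement. It does not say that. It is silent on missing values, and a full protocol or analysis plan that is not shown could supply imputation. This stands: the limitation belongs to the test as named, and the absence of a missing-data rule in an article is not itself a fault.

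**The sizing proves nothing about the analysis set.** It is tempting to read 720 to 800 as confirmation that 720 will be analysed. Dividing by 0.9 is ordinary planning; it protects information and does not define who is analysed. This stands in full.

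**The t test is not the only analysis named.** Cluster-level and multilevel analyses are mentioned, and the multilevel models might use repeated readings. This stands as far as it goes, but the article does not say that they do, and the 1-year two-sample comparison is the only test it specifies.

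**Referral is not loss.** The Follow-up plan intends to use referral to strengthen follow-up, so nothing shows that referred patients lose their 12-month reading. This stands; referral is a possible route to missing data and no more.

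**The bias is small, and the demonstration favours the remedy.** A shift of 0.6 mmHg is about one-seventh of a 4 mmHg standard error. Regression on month-6 pressure recovers 10 because the assumed loss depends on that reading alone. Where the lost patients simply had no benefit, a mixed model corrects only as far as their earlier readings show it. This stands and limits the weight of the point. It does not make the single-time-point test the better choice when the earlier readings are scheduled anyway.

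**Conclusion.** The point holds as a matter of analysis choice. For an outcome scheduled serially in both arms, the article names a single-time-point test that, as named, leaves out about 80 of 800 patients and their earlier readings. It does not hold as a contradiction of intention to treat or as an error in the sample size.

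The likely size is modest: about 0 to 0.6 mmHg on a 10 mmHg target under mild assumed dependence, and up to about 2 mmHg if the highest tenth at month 6 were all lost. These figures rest on 10% loss, SD 20 and effect 10 from the article, and on an assumed loss mechanism, month-6 difference and correlation between visits. The gain in power is negligible. The change is worth making because it is cheap and needs a weaker assumption about loss than the named test does.

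**What to change.** Make the primary analysis a linear mixed model on blood pressure at the visits common to both arms: baseline and months 3, 6 and 12. Leave out the monthly readings, because the Follow-up plan says that control participants are measured less often. Specify:

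- baseline blood pressure, either as a covariate or as an outcome with a mean common to both arms; only the second form lets patients lost before month 3 contribute;
- arm-by-visit terms and a patient-level covariance across visits;
- a random effect for health centre. If baseline is modelled as an outcome, let this effect vary by visit, since a single centre intercept assumes that centres do not differ in their change;
- a small-sample degrees-of-freedom correction for eight clusters, such as Kenward-Roger;
- the month-12 arm contrast as the primary estimate.

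Keep the comparison of observed 12-month values as a sensitivity analysis, and say in one sentence how patients without that reading are handled under intention to treat.

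**Cost.** Analysis wording and slightly more analysis work, with no added visits or measurements. The model relies on missing at random. It also implies a month-12 blood pressure for patients who die, which the report should acknowledge.
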